## Abstract

**Background:**

*Xingnao Kaiqiao* acupuncture involves needling of the *Neiguan* (PC6), *Renzhong* (DU26), and *Sanyinjiao* (SP6) acupoints. The technique has a significant clinical effect in many neurological diseases. In the present report, we have developed a protocol for a scientific trial to analyze whether *Xingnao Kaiqiao* can be used to treat gastrointestinal dysfunction after laparoscopic surgery. In this context, we intend to execute a double-blind, randomized controlled trial to assess the efficacy and safety of *Xingnao Kaiqiao* acupuncture via intradermal needling.

**Methods/design:**

This will be a single-center, double-blind, randomized controlled clinical trial. It has been designed on the basis of the Consolidated Standards of Reporting Trials (CONSORT 2010) guidelines and the Standards for Reporting Interventions in Controlled Trials of Acupuncture (STRICTA). The subjects will be recruited from among inpatients scheduled for laparoscopic surgery at the Department of Minimally Invasive Surgery, Tianjin Nankai Hospital, Tianjin, China. Using random numbers generated in SPSS 19.0, the recruited subjects will be allocated to either the “*Xingnao Kaiqiao*” group or the sham stimulation group. A specially appointed investigator will be in charge of the randomization. *Xingnao Kaiqiao* via intradermal needling (or sham needling) will be administered 6 h after laparoscopic surgery, and then every 12 h for a total of six sessions, each of which will last 3 min. The subjects will undergo their first evaluation shortly before the first treatment (6 h after laparoscopic surgery); evaluations will be repeated every 12 h until a total of seven evaluations have been completed. The primary outcome will be the time until the first postoperative flatus. The secondary outcomes will be: the time until the first postoperative defecation; levels of abdominal pain, abdominal distension, and nausea; blood ghrelin level; occurrence of vomiting; psychological status; and quality of life.

**Discussion:**

This upcoming randomized clinical trial was designed as a standardized method to assess the efficacy and safety of *Xingnao Kaiqiao* acupuncture using intradermal needles on PC6, DU26, and SP6 in the treatment of gastrointestinal dysfunction after laparoscopic surgery. We aim to provide evidence and thus improve the clinical application of this technique.

**Trial registration:**

Chinese Clinical Trial Registry, ChiCTR-IOR-17010763. Registered on 2 March 2017.

**Electronic supplementary material:**

The online version of this article (doi:10.1186/s13063-017-2319-3) contains supplementary material, which is available to authorized users.

## Background

Gastrointestinal dysfunction frequently occurs after abdominal surgery [1] and can lead to the accumulation of gastrointestinal secretions and gas. Thus, patients have trouble passing flatus and defecating, and this causes abdominal distension, abdominal pain, nausea, and vomiting. These symptoms affect postoperative recovery [2]. Severe cases can result in further complications, such as intestinal adhesions and obstructions, which affect patients’ quality of life. Currently, Western medicine treats postoperative gastrointestinal dysfunction using alvimopan. However, the side effects of this drug, which include nausea and vomiting, limit its widespread use [3]. In the case of abdominal surgery, successful postoperative rehabilitation would promote the early recovery of gastrointestinal function and minimize side effects [4].

Acupuncture has long been used in traditional Chinese medicine to treat gastrointestinal diseases, and considerable accumulated experience has highlighted its efficacy and advantages. Indeed, in 1997, the US National Institutes of Health published a consensus statement declaring that acupuncture can be an effective treatment for postoperative nausea and vomiting [5]. More recent research has shown that acupuncture promotes the recovery of gastrointestinal function after surgery [6–8]. These results have allowed practitioners to improve their use of acupuncture to treat postoperative gastrointestinal dysfunction.

Other research has shown that peripheral ghrelin is largely responsible for regulating gastrointestinal function, and that ghrelin in the central nervous system can influence gastrointestinal physiological activity [9]. High concentrations of ghrelin are found in the cell bodies and synapses of the hypothalamus, pituitary gland, and gastrointestinal vagus nerve [10, 11]. Therefore, it may be that acupuncture regulates gastrointestinal function by stimulating nerves, especially the vagus nerve. Specifically, the stimulation of acupoints may promote the release of ghrelin in both the central and peripheral nervous system. By way of comparison, one study reported that transcutaneous electrical stimulation of *Zusanli* (ST36) may alleviate limb muscle spasms caused by stroke-induced injury to motor neurons [12]. It is believed that this effect is mediated by neurotransmitters. Another study reported that acupuncture causes chain reactions in the peroneal and tibial branches of the sciatic nerve [13]. The same study showed that electrostimulation of ST36 stimulates the peroneal nerve, which then propagates the impulse through the sciatic nerve to the vagus nerve, causing the release of aromatic l-amino acid decarboxylase and leading to elevated levels of neurotransmitters. Similarly, electrostimulation of *Neiguan* (PC6) stimulates sensory fibers in the median nerve, which in turn excite the nucleus tractus solitarius of the vagus nerve causing neurotransmitter release [14]. In vagotomized patients, the central effects of ghrelin are blocked, indicating that vagus nerve stimulation promotes ghrelin release [15].

In 1972, [name], a member of the Chinese Academy of Engineering, suggested that *Xingnao Kaiqiao* acupuncture (XNKQAT) can be used to treat encephalopathy. XNKQAT involves the use of needling acupoints to activate the brain’s nourishment of the liver and kidneys, as well as to promote the *flow of qi*. The principal acupoints of this technique are PC6, *Renzhong* (DU26), and *Sanyinjiao* (SP6). Since its inception 40 years ago, the application of XNKQAT has gradually been improved through clinical practice, clinical trials, and laboratory research, and it is used to treat a continuously expanding spectrum of diseases.

XNKQAT can be applied using different acupuncture methods, such as needling, acupressure, electroacupuncture, moxibustion, and others. Of these, intradermal needling is now commonly used; using this method, practitioners must accurately locate the correct acupoints to ensure that patients are treated effectively. However, few studies have reported successful treatment of postoperative gastrointestinal dysfunction using intradermal needling. Therefore, this article proposes a rigorously designed, double-blind, randomized controlled clinical trial to investigate the efficacy and safety of intradermal needling-based XNKQAT to treat gastrointestinal dysfunction after laparoscopic surgery. The trial is designed to provide high-quality scientific evidence that will promote the clinical application of XNKQAT.

A pilot trial has been conducted in six patients who underwent laparoscopic surgery. These subjects were randomly assigned to the “XN group” (XNKQAT) or the “SH group” (sham stimulation). The patients adhered strictly to the evaluation and treatment processes of this study, and we observed that XNKQAT via intradermal needling of PC6, DU26, and SP6 is effective in the treatment of gastrointestinal dysfunction after laparoscopic surgery. Specifically, the average time until the patients’ first postoperative flatus was shorter in the XN group (15.21 ± 2.89 h) than in the SH group (28.32 ± 4.31 h). This supports the hypothesis that XNKQAT via intradermal needling promotes the recovery of gastrointestinal function after laparoscopic surgery.

## Methods/design

### Design

This is a protocol for a double-blind, single-center, randomized controlled clinical trial that conforms to the Consolidated Standards of Reporting Trials (CONSORT 2010) guidelines (Fig. 1), as well as to the Standards for Reporting Interventions in Controlled Trials of Acupuncture (STRICTA) [18, 19]. We designed the trial on the basis of the Standard Protocol Items: Recommendations for Interventional Trials (SPIRIT) statement (Fig. 2) and its corresponding checklist (Additional file 1). Two groups will be tested in parallel and compared. The trial participants will be selected from among subjects who are to receive laparoscopic surgery in the Department of Minimally Invasive Surgery, Tianjin Nankai Hospital, Tianjin, China, between March and June 2017. The XNKQAT intradermal needling will be carried out by specialist nurses with at least 5 years of professional training in acupuncture.

**Fig. 1 Fig1:**
[figure not shown]
CONSORT 2010 flow diagram. *SH* sham, *XN Xingnao Kaiqiao* acupuncture technique

**Fig. 2 Fig2:**
[figure not shown]
The schedule of enrollment, interventions, and assessments. *-t*
_*1*_ the day before the surgery, *t*
_*0*_ the day of the surgery, *t*
_*1*_
*-t*
_*6*_ the days in hospital after the surgery, *t*
_*7*_ the day of the discharged, *t*
_*8*_ 14 days after the discharged, *t*
_*9*_ 30 days after the discharge, *SH* sham, *XN Xingnao Kaiqiao* acupuncture technique

Using random numbers generated in SPSS 19.0, we will allocate subjects to either the XN group or the SH group at a ratio of 1:1. To reduce selection bias, a specifically appointed investigator will be in charge of the random allocation and other confounding factors. The first XNKQAT treatment will take place 6 h after surgery and will be followed by another treatment every 12 h thereafter until a total of six treatments have been completed. Each treatment will last 3 min. The patients will subsequently attend three follow-up visits. In addition, seven evaluations will be performed to monitor outcomes related to the recovery of gastrointestinal function. The first such evaluation will take place immediately before the first treatment, 6 h after surgery. The evaluations will be repeated every 12 h thereafter until a total of seven evaluations have been completed.

### Study subjects

The study will recruit inpatients of the Department of Minimally Invasive Surgery, Tianjin Nankai Hospital, Tianjin, China, who are scheduled to undergo laparoscopic surgery between March and November 2017. Based on the six-subject pilot trial described above, which was performed in November 2016, the present trial will compare the time until first postoperative flatus between the two groups; we consider this the primary outcome in the recovery of gastrointestinal function. In addition, the pilot trial’s intervention was based on that of the present formal trial. The treatment in the pilot trial was needling (or sham needling) at PC6 on both forearms, SP6 on both ankles, and DU26; that is, at a total of five acupoints. Using the parameters α = 0.05 and power = 80%, and assuming a dropout rate of 15%, 34 participants will be required to participate in the full-scale study to ensure statistically meaningful results.

To ensure that the results are accurate, the present study will include strict inclusion, exclusion, and elimination criteria, as outlined below.

#### Inclusion criteria

To enroll in the trial, subjects must: 1) be aged 18–65 years; 2) be scheduled to undergo elective laparoscopic surgery under general anesthesia; 3) have no experience with intradermal needling therapy; 4) not be enrolled in any other clinical trials; 5) have no cognitive dysfunction, aphasia, mental illness, or other communication barriers; and 6) be able to sign an informed consent form.

#### Exclusion criteria

Subjects may not participate in the trial if they: 1) are pregnant or lactating; 2) have a history of abdominal surgery; 3) are to receive surgery other than laparoscopic surgery during their hospital stay; 4) have skin injuries at the selected acupoints; 5) are allergic to adhesive tape; 6) have severe gastrointestinal disease or chronic pain (e.g., chronic pelvic pain); 7) have been taking analgesic drugs for a long time or in the last 48 h; 8) have a serious cardiac, encephalic, hepatic, renal, or hematologic system disease; 9) have a history of substance (such as morphine) abuse, exercise-induced vomiting, diabetes, surgical vomiting, or obesity (body mass > 80 kg); or 10) have been bedridden for a long time.

#### Elimination criteria

Subjects will be eliminated from the trial if: 1) their laparoscopic surgery is changed to laparotomy; 2) they refuse to undergo the treatment for any reason; 3) serious syndromes, such as biliary fistula or peritonitis, arise during the treatment; 4) they transfer to another specialist for treatment; 5) they become comatose or die; 6) they are unable to attend the follow-ups for any reason; 7) they do not match the inclusion criteria and were accidentally included; and 8) they do not comply with the treatment or fail to provide information that may be important in the evaluation.

### Ethical issues

The Institutional Review Board (IRB) of Tianjin Nankai Hospital approved the trial on 10 February 2017 (IRB approval no. 2016-037P). After obtaining the IRB approval, we registered the trial on an authoritative registration platform of clinical trials (Chinese Clinical Trial Registry, ChiCTR-IOR-17010763) before the start of the study. The informed consent form (Additional file 2) was developed in accordance with the Declaration of Helsinki. All qualified patients can choose freely whether they wish to participate in the trial; those who do will be required to sign an informed consent form before enrolling.

### Randomization

Patients will be assigned in a 1:1 ratio to either the XN group or the SH group using random numbers generated in SPSS 19.0. To reduce selection bias and avoid other confounding factors, a specifically appointed investigator will be in charge of the randomization process. When recruiters identify a subject who meets the criteria for participation, they will obtain a sequence number for that subject from the researcher in charge of the randomization process.

To prevent the biases of the researchers from influencing the authenticity of the clinical findings, the subjects’ group allocations will be concealed from the recruiters and evaluators using the sealed envelope method. Briefly, the subjects’ allocation will be concealed inside sealed, opaque, serialized envelopes from the researchers responsible for recruitment and treatment evaluation. To ensure strict confidentiality, the envelopes will not be transparent, even under intense light. To prevent confusion around the group assignments, the subjects’ full names and birthdates will be written on the outside of their envelopes using carbon paper. The information on the sealed envelopes, and the details about the subjects, will be video-recorded, and the carbon copy of the label on the outside of the sealed envelope will then be attached to the group allocation card inside the envelope. Next, another researcher will check the videos to ensure the subjects’ envelopes are sealed. The entire process of opening the envelopes will also be video-recorded. The envelopes will be opened, and the assigned intervention type (XNKQAT or sham) will only be known after the respective subject has undergone all baseline evaluations.

### Blinding methods

This will be a double-blind trial. The subjects, evaluators, and statisticians will be unaware of the group assignment; that is, researchers evaluating the individual outcomes will be unaware of the group allocations, as will the statistician analyzing the data. It follows that the duties of the operators, data administrators, evaluators, and statistician will be mutually exclusive.

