### Intervention

After laparoscopic surgery, the subjects will be asked to lie in the supine position without a pillow, and without eating or drinking. They will begin a liquid diet on the second day after surgery. The two groups will receive XNKQAT intradermal needling or sham stimulation 6 h after the surgery. Treatment will be repeated every 12 h thereafter until a total of six treatments have been administered. Each treatment will last for 3 min. Each time, the intradermal needles (or sham needles) will be attached to the surface of the acupoints. Six hours after surgery, immediately before the first treatment, the first evaluation will be carried out. The subjects will be evaluated every 12 h thereafter until a total of seven evaluations have taken place. Acupoints will be located in accordance with the World Health Organization Standard Acupuncture Point Locations in the Western Pacific Region [20]. The acupoints used will be PC6, DU26, and SP6. The nurse administering the treatment will stand next to the subject’s bed and help them to find a comfortable supine position.

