### Treatment (XNKQAT) group

This group of subjects will receive XNKQAT intradermal needling treatment at PC6 on both forearms, at SP6 on both ankles, and at DU26; that is, at a total of five acupoints (Fig. 3). After standard disinfection of the acupoints with 75% ethanol solution, the nurse will position the disposable medical intradermal needles (0.22 mm diameter × 1.5 mm length) perpendicular to the skin at the subject’s acupoints and then needle them into the skin. During the approximately 3-min treatment, the nurse will alternatively press the five intradermal needles for 15 s; a 20-s pause will occur between the repeated pressing intervals. To avoid injury to the skin or infection at the acupoints, the needles will not be twisted. The subject should feel a prick at the needled location. This study will use a visual analogue scale (VAS; Fig. 4) for pain [20] to determine the needle pressing force. Based on the VAS evaluation performed in the pilot trial, the pressing force will be limited to 40 mm. More importantly, in the XNKQAT, the manipulation standard of DU26 stimulation is “moistening of the eye,” that is, tear production (Fig. 5). Since the subjects will undergo a long pre-operative fasting period, excitation of the acupoints may trigger a hypoglycemic response. Therefore, it will be important to monitor the subjects’ faces during treatment to ensure they do not become pale or apathetic. If these signs occur, treatment will be stopped, the subjects’ blood glucose will be tested immediately, and appropriate management will be performed.

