### Control (sham) group

In the SH group, the acupoints will be selected as described above. Based on the successful pilot trial, the nurse will use adhesive tape that is similar to intradermal needle tape at the acupoints described above. However, they will not use needles or press the points. The number of sessions, and the duration of treatment, will match the procedure in the XN group. To ensure that subjects in the SH group feel fully cared for, they will be provided with health-related information and support (complication awareness, dietary direction, exercise training, and psychotherapy), and they will be more verbally engaged than the treatment group.

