##### Primary outcome

The time until the first postoperative flatus will be calculated, beginning at the time the subject returns to the ward after surgery. The subjects and their family members will be told to keep a record of the time until the first postoperative flatus:

Time until the first postoperative flatus = the moment of the first postoperative flatus – the moment when the subject returned to the ward after surgery

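### The protocol states that subjects are blinded, but the described sham is unlikely to keep them so, and subjects and families record the primary outcome

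*Protocol article*

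**What the plan says.** The abstract, the end of the Background, the Design section and the Blinding methods section all call the trial double-blind. Blinding methods gives the content of the claim: "The subjects, evaluators, and statisticians will be unaware of the group assignment". The explanation that follows it covers only the outcome evaluators and the statistician.

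In the Treatment (XNKQAT) group section, intradermal needles are placed "perpendicular to the skin at the subject’s acupoints and then needle them into the skin", at five acupoints. "The subject should feel a prick at the needled location". During each session of about 3 min, "the nurse will alternatively press the five intradermal needles for 15 s", with 20 s pauses. A pain visual analogue scale governs the pressing, and "the pressing force will be limited to 40 mm". The manipulation standard at DU26 is tear production.

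In the Control (sham) group section, the nurse applies tape resembling the needle tape at the same points. "However, they will not use needles or press the points". Number and duration of sessions match the active arm. Sham subjects also receive health information and support, and are to be engaged verbally more than the treatment group.

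The Intervention section, covering both arms, says: "Each time, the intradermal needles (or sham needles) will be attached to the surface of the acupoints".

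Under Primary outcome: "The subjects and their family members will be told to keep a record of the time until the first postoperative flatus". Time to first defecation is recorded in the same way. For abdominal pain, distension, nausea and vomiting, subjects and families assist in keeping the record.

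**The concern.** Subject blinding requires that a subject cannot readily tell the arms apart from what is done to them. Here the active procedure is meant to be felt and to produce a visible sign, and the sham as specified reproduces neither. The Background itself says that only strong, sustained stimulation at DU26 produces tears.

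This matters because of where the primary data come from. First flatus is noticed and timed by the subject, with family help. A blinded evaluator who receives a time from a subject who has guessed the arm cannot remove whatever that guess did to the noticing or recording. If masking fails, the contrast contains needling together with expectation, reporting and attention differences, but would be published as a double-blind effect. The Discussion says the results will determine whether the treatment should be applied more widely.

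**Working it through.** **1. The arms side by side.**

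| Feature | Active arm | Sham arm | Alike to the subject? |
|---|---|---|---|
| Tape at the acupoints | Needle tape | Similar tape | Yes |
| Number and duration of sessions | Six, about 3 min each | Matched | Yes |
| Skin penetration | Yes, five points | No needle | No |
| Prick | Should be felt | No source for it | No |
| Pressing | 15 s presses, limited on a pain scale | None | No |
| Tears at DU26 | Manipulation standard | No stimulus for it | No |
| Verbal engagement and support | Less | More | No |

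The matched features are appearance and schedule. The unmatched ones are those a subject feels. Inclusion criterion 3 (no experience of intradermal needling) removes prior knowledge of the sensation, but does not make pricking, pressing and tears resemble untouched tape.

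**2. Who is protected.** The statistician's blinding is untouched by the sham design. The evaluators' blinding is exposed only indirectly, through what subjects or families say. The times to first flatus and first defecation originate with subjects and families, so evaluator blinding does not cover them.

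**3. How much treatment precedes the primary event.** Sessions start at 6 h after surgery and repeat every 12 h: 6, 18, 30, 42, 54 and 66 h. The six-patient pilot gave mean times to first flatus of 15.21 h (active) and 28.32 h (sham), counted from return to the ward. If return to the ward closely follows surgery, the active mean falls after one session (6 < 15.21 < 18) and the sham mean after two (18 < 28.32 < 30). A treatment guess taken after the sixth session would therefore come well after the primary event, when recovery itself may influence the answer.

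**4. The plan's own figure, and an illustration.** The sample size reproduces: n = (1.96 + 0.84)² × (2.89² + 4.31²) / 4² = 7.84 × 26.9282 / 16 = 13.19, rounded up to 14. Then 14 / 0.85 = 16.5, rounded up to 17 per group, 34 in total. This point does not change it.

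To see how sensitive a trial of this size is to a recording difference between arms, assume no true effect, the planning SDs and 17 per group. The standard error is √(26.9282 / 17) = 1.26 h. For an assumed shift of b hours, the two-sided rejection probability by normal approximation is Φ(b/SE − 1.96) + Φ(−b/SE − 1.96):

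| Assumed shift b | 17 per group | 14 per group |
|---|---|---|
| 0 h | 0.050 | 0.050 |
| 1 h | 0.125 | 0.111 |
| 2 h | 0.356 | 0.303 |
| 3 h | 0.664 | 0.581 |

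The shifts are assumptions. The article gives no value, and nothing in it shows that any of these is likely.

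**The case against.** The best defence is that masking was attempted. Subjects must be new to the technique, the tape looks similar, and acupoints, sessions and duration match. What subjects are told about the two arms is in the consent form, which is not shown. A subject who does not know what needling should feel like might accept tape as treatment. This stands to the extent that a reader might infer that subjects are certainly unmasked; the article does not document that. It supports only that masking is unlikely to hold.

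Other stronger readings also fail:

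- **A known bias favouring needling.** No size is given. The extra information, psychotherapy, exercise training and verbal engagement in the sham arm could work against the needling arm, so even the net direction is open.
- **Symptom records produced by families.** The article says subjects and families assist, and evaluators carry out the clinical evaluations. The point about recording is firm only for the flatus and defecation times.
- **A proven contradiction over the sham device.** The mention of sham needles in the general Intervention section may be loose shorthand for the tape. It needs reconciling, but it does not establish two different shams.
- **No check of masking as a defect in itself.** A journal article may leave that to the full protocol. It appears below as a remedy only.

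**Conclusion.** The point holds against the stated claim of subject blinding. The article asserts that subjects will be unaware of their group, and its descriptions of the two procedures make that unlikely despite the needle-naive criterion and the similar tape. Because subjects and families time the first flatus, blinded evaluators and a blinded statistician do not protect the primary comparison. The size and net direction of any resulting bias cannot be estimated from the document, and the illustration shows only that a trial of 34 is sensitive to shifts of an hour or two if they occurred. The conclusion assumes that the procedures are carried out as written and that the unseen consent wording does not somehow make the two experiences indistinguishable. What changes is the description of the trial and what its result can be said to show, not the sample size or the test.

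**What to change.** 1. In the abstract, Design and Blinding methods sections, and wherever else the label appears, describe the trial as evaluator- and statistician-blinded, with subject masking attempted but not assured.
2. Reconcile the Intervention section (sham needles) with the Control (sham) group section (no needles), so that a reader knows what the control device was.
3. Add one treatment-guess question to the case report form for every subject, asked soon after the first session and before first flatus where possible. A later repeat is secondary, because recovery may influence it. Add one such question for the evaluators.
4. Report the guesses by arm beside the primary result.
5. Word the conclusion as the effect of needling plus possible expectation, reporting and attention differences.

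The cost is one extra question at existing contacts, some rewording, and the loss of the unqualified double-blind label. Recruitment is ongoing, so the question should be added promptly: early guesses cannot be collected reliably afterwards.
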